### Study Hypotheses

Our main hypothesis is that the SWADOC is reliable and valid.

Our second hypothesis is that the subscores (oral phase and pharyngeal phase) and the total score are related to the patient's level of consciousness. Moreover, based on previous studies (13, 15), we expect that UWS patients will be at level 0 for oral phase items 1, 3, and 4 of the SWADOC-scored: no mouth opening at spoon approach, no spontaneous lip prehension, and no appropriate tongue propulsion.

### Data Analysis

The statistical significance will be set at *p* < 0.05.

#### Power of the Study

The sample size was calculated using a power calculation (G * Power, Universities of Kiel, Mannheim, and Düsseldorf) in a one-way analysis of variance (ANOVA) with a significance level of 0.05 and a power of 0.8. Effect size is based on previous published data on swallowing performance in patients with DOC (13). Cohen's *d* was used to estimate the effect size; the result was 0.659, corresponding to an eta-squared of 0.0979. We round up and base our calculation on an effect size of 0.1, corresponding to an intermediate effect. In this context, a total sample size of 104 participants (26 per group) is needed to demonstrate a difference in SWADOC‘ subscores and total score between the four consciousness groups. If, by the end of June 2025 the sample size is not reached, we will discuss extending the data collection period if necessary.

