In daily practice, speech therapists help document the presence or absence of a range of components required for swallowing in order to guide therapy and monitor its effectiveness by repeated assessment over time. The clinical reality of patients with DOC, mainly the lack of response to simple motor commands (in UWS and MCS–) and functional communication, makes it difficult to fully understand and appropriately treat their swallowing disorders. For these reasons, classical swallowing assessment at the bedside can be unsuitable for this population. There is a lack of appropriate bedside tools to appraise and monitor swallowing disorders in patients with DOC. The impossibility of orienting interventions based on determined quantitative and qualitative swallowing components makes it more difficult to develop a treatment plan and assess the patient's progress.

Our recent DOC cohort study (13) found some links between swallowing and the level of consciousness. In particular, none of the patients with UWS and only a minority of the patients in MCS exhibited an effective oral phase of swallowing (adequate lip prehension, tongue propulsion, and no post-swallowing oral stasis). However, these links are not yet completely understood, and further studies are necessary to increase our knowledge of which components of swallowing are linked to consciousness and to what extent. In this context, the validation of a tool that focuses on qualitative and quantitative swallowing components will help us identify swallowing behaviors that may be considered unequivocal signs of consciousness in patients with DOC. These results may eventually contribute to the development of new diagnostic guidelines for DOC that would include swallowing behaviors in their criteria.

The aim of this article is to present a protocol that develops and validates the SWallowing Assessment in Disorders Of Consciousness (SWADOC). This tool will be administered repeatedly to a population of patients with DOC by different examiners, and intrinsic test characteristics will be calculated. The relationship between patients' level of consciousness and SWADOC scores will also be studied.

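### The 80% power claimed for 104 patients does not follow from the cited d = 0.659, because a two-group conversion is carried into a four-group ANOVA

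*Protocol article*

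**What the plan says.** The Power of the Study section plans for a "one-way analysis of variance (ANOVA) with a significance level of 0.05 and a power of 0.8". The effect size is attributed to published swallowing data from an earlier cohort of patients with disorders of consciousness. For Cohen's d, "the result was 0.659, corresponding to an eta-squared of 0.0979". The section continues: "We round up and base our calculation on an effect size of 0.1, corresponding to an intermediate effect". It concludes that "a total sample size of 104 participants (26 per group) is needed to demonstrate a difference" in the SWADOC subscores and total score between the four groups, which are UWS, MCS–, MCS+ and EMCS (Population and Recruitment).

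The section does not say which two groups d compares, on which outcome, or what the four group means are assumed to be. The only UWS-to-MCS finding that the article reports from that cohort is in the Introduction: "none of the patients with UWS and only a minority of the patients in MCS exhibited an effective oral phase of swallowing". EMCS is not mentioned there.

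**The concern.** Cohen's d is a distance between two means. An omnibus ANOVA over four groups is powered on f, the standard deviation of the four means divided by the within-group SD. One distance does not fix f for four groups, because the position of the other means matters. The article moves from d to eta-squared as if there were two groups, and then tests four.

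This is the only justification given for the sample size. It supports the second hypothesis, that swallowing scores are related to level of consciousness. If the result is null, readers will weigh it against a stated 80% power, and that figure has not been derived from the evidence cited for it.

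**Working it through.** **Inputs, all from Power of the Study except the group count:** alpha 0.05; target power 0.80; d = 0.659; eta-squared 0.0979, rounded to 0.1; N = 104, 26 per group; four groups (Population and Recruitment).

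**Method.** Noncentral F with 3 and 100 df and noncentrality λ = N·f², where f² = η²/(1 − η²). With equal groups, f is also the root mean squared deviation of the four means from their average, in SD units.

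**1. The plan's own figure.** η² = 0.1 gives f² = 0.1/0.9 = 0.111, f = 0.333 and λ = 104 × 0.111 = 11.56. Power is 80.8%, and 104 is the smallest multiple of four that reaches 80%. The stated N reproduces.

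**2. The conversion.** 0.659² = 0.4343, and 0.4343/(0.4343 + 4) = 0.0979. This matches the printed value and is the formula for two equal groups, equivalent to f = d/2 = 0.3295.

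**3. The rounding.** η² = 0.0979 gives 79.8% power at 104, and 108 patients in equal groups for 80%. Rounding up is slightly favourable but minor.

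**4. Assumption A: 0.659 SD is the distance between the lowest and highest of the four means.** Means are in units of d.

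| Pattern | f | η² | Power at 104 | N for 80% |
|---|---|---|---|---|
| 0, ½, ½, 1 (middle groups halfway) | 0.233 | 0.051 | 47.5% | 208 |
| 0, ⅓, ⅔, 1 (equal steps) | 0.246 | 0.057 | 52.1% | 188 |
| 0, 1, 1, 1 (one versus three) | 0.285 | 0.075 | 66.3% | 140 |
| 0, 0, 1, 1 (two versus two) | 0.3295 | 0.0979 | 79.8% | 108 |

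Under this assumption only the two-versus-two split gives f = d/2.

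**5. Assumption B: 0.659 SD is a UWS-versus-MCS distance and EMCS lies further out.**

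| Pattern (UWS, MCS–, MCS+, EMCS) | f | Power at 104 |
|---|---|---|
| 0, 1, 1, 1.5 | 0.359 | 86.8% |
| 0, ½, 1, 1½ (d is UWS to MCS+, equal steps) | 0.368 | 88.6% |
| 0, ⅔, 1⅓, 2 (d is UWS to the MCS average, equal steps) | 0.491 | 99.1% |

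**6. What 104 patients can detect.** Omnibus power of 80% needs f ≈ 0.33. With equal steps f = spread × √(5/36), so the UWS-to-EMCS spread must be 0.33/0.3727 ≈ 0.89 SD.

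**7. A linear contrast (1 and 100 df) over the ordered groups, under assumption A.** Power is 70% against 52% for the omnibus test with equal steps, but 61% against 66% if only UWS differs from the rest.

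**The case against.** The strongest reply is that the stated figures agree with one another: the conversion is right for two groups, and eta-squared 0.1 does give 104. That stands. The fault lies in the step between them, where a two-group value becomes the input to a four-group test.

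A reader might go further and infer that the study really has only about 47% to 66% power, and that the plan relies on a best-case pattern. The documents do not support this. Those figures need 0.659 SD to be the full UWS-to-EMCS spread, which the article never says. The Introduction reports UWS and MCS patients only, so a UWS-versus-MCS contrast is at least as compatible with the text, and step 5 then puts power above the claim. Two-versus-two is the most favourable pattern only when the full spread is capped at d.

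A reader might also say that a two-versus-two split contradicts a graded relation that the study expects. Study Hypotheses says only that the scores are related to level of consciousness, and singles out UWS on three oral items. It states no equal steps and no monotone order over four groups. It remains true that nothing in the article supports a two-versus-two split either.

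Finally, 0.0979 might have begun as a multi-group eta-squared that was re-expressed as d, in which case the step would be harmless. The section describes the opposite direction, from d to eta-squared.

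**Conclusion.** The power statement is wrong as written: 80% at N = 104 does not follow from d = 0.659. It follows from eta-squared 0.1, which four groups would have only under a pattern of means that the article does not give. Under the two readings shown, power runs from about 47% to about 99%. Both readings are assumptions, so neither a shortfall nor a surplus is established. The arithmetic from eta-squared 0.1 to 104 is sound.

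This should be fixed, but it does not threaten the study. It concerns the second hypothesis, while the main one is the reliability and validity of the tool. The omnibus ANOVA with Tukey comparisons, or its rank-based alternative, is a valid analysis, and the lack of a trend test is not an error.

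**What to change.** Keep N = 104 and rewrite the justification in Power of the Study in one of two ways:

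- State which groups and which outcome d = 0.659 compares, give the four assumed means and a common SD, and replace the 80% claim with the power that those means yield.
- Drop the link to d and state the detectable effect: with 26 per group, about 80% power for f ≈ 0.33 (eta-squared 0.10), for example a UWS-to-EMCS spread of about 0.89 SD in equal steps.

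Either way the cost is a few sentences and perhaps a less favourable stated power. No extra patients are needed.

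Optionally, add a linear contrast over the ordered groups as a supporting analysis. As step 7 shows, it gains power if the means rise in equal steps and loses some if only UWS differs, so it should not replace the omnibus test without a stated reason.

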#### Descriptive Analysis

First, descriptive statistics will be performed to describe the entire group and each diagnostic group (UWS, MCS–, MCS+, and EMCS) for age, gender, etiology, and time since insult. To test gender independence between groups, we will use chi-square tests. For the other variables, we will perform a one-way ANOVA with group as an independent variable. Homogeneity of variance will be assessed using Levene's test. In case of violation, we will use Welch's approximation of a ANOVA.

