### Population and Recruitment

This study will be carried out in patients with DOC or emerging from DOC following severe acquired brain injury. Patients will be divided into four groups according to their clinical diagnosis, as assessed with the SECONDs and with the CRS-R: UWS, MCS–, MCS+, and EMCS. Participants will be recruited from inpatient neurological rehabilitation programs in post-coma units and rehabilitation services or among patients hospitalized for a multimodal assessment of consciousness for diagnostic and prognostic purposes.

Only patients who meet all of the following inclusion criteria will be considered for enrollment: (1) age above 18 years; (2) perfect knowledge of French language before the injury; (3) previous coma phase caused by a severe acquired brain injury; (4) medical stability (no mechanical ventilation or sedation, no acute medical pathology such as infection or respiratory distress); (5) no neurological or otorhinolaryngological disease that can impact swallowing prior to the brain injury; (6) minimum of 28 days since the acquired brain injury at inclusion (28, 29); (7) diagnosis of UWS, MCS–, MCS+, or EMCS based on the SECONDs and the CRS-R; (8) informed consent from the patient's legal representative; and (9) affiliated patient or beneficiary of a health insurance plan (for participants in France only).

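### As written, the Descriptive Analysis section assigns a one-way ANOVA to etiology, a nominal variable; with three or more categories the p-value depends on how they are numbered (minor)

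*Protocol article*

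**What the plan says.** The Descriptive Analysis section promises descriptive statistics for the whole sample and for "each diagnostic group (UWS, MCS–, MCS+, and EMCS) for age, gender, etiology, and time since insult". It then assigns tests:

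- Gender: "To test gender independence between groups, we will use chi-square tests".
- Everything else: "For the other variables, we will perform a one-way ANOVA with group as an independent variable".
- Unequal variances, as judged by Levene's test: "In case of violation, we will use Welch's approximation of a ANOVA".

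Taking gender out of the list of four leaves age, etiology and time since insult under the ANOVA. Etiology otherwise appears only indirectly, in the inclusion criterion under Population and Recruitment: "previous coma phase caused by a severe acquired brain injury". The article does not define etiology categories, say how many there are, put them on a numeric scale or give etiology a categorical test elsewhere. The general significance rule in Data Analysis is "The statistical significance will be set at *p* < 0.05".

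**The concern.** The cause of a brain injury is a label. ANOVA compares group means, and Levene's test and Welch's version also need a numeric outcome. To run any of them on etiology, someone must number the categories, and the mean of those numbers has no meaning. With three or more categories, renumbering changes the spacing and order of the codes, and with them the F statistic, although no patient has changed.

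This is more than a detail left out of a condensed article. The article names a test for this variable, and the test named does not suit it. At stake is the p-value that says whether the four consciousness groups differ in etiology: it could point to a difference or to none depending on the numbering.

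**Working it through.** **Inputs.** From the article: four groups, 26 per group, 104 in total (Power of the Study), and a 0.05 significance level (Data Analysis). The article states no figure for this comparison. Its one computed figure, the sample size, is not in dispute and reproduces: with eta-squared 0.1, f = √(0.1/0.9) = 0.333, and a four-group ANOVA at N = 104 has power 0.808. All etiology counts below are **assumed**.

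**Method.** For each assumed table of group by etiology, compute (a) the Pearson chi-square, which does not depend on codes, and (b) the one-way ANOVA on integer codes, repeated for every assignment of codes to categories.

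**Table 1, four categories** (rows are groups): 6/14/4/2, 10/8/5/3, 14/4/6/2, 13/5/3/5.

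- Chi-square on (4−1)(4−1) = 9 degrees of freedom: p = 0.104.
- ANOVA over 4! = 24 codings: p from 0.013 to 0.874; 8 of 24 fall below 0.05 and 16 do not.
- Column totals are 43, 31, 18 and 12, so expected counts are 43/4 = 10.75, 31/4 = 7.75, 18/4 = 4.5 and 12/4 = 3.0. Half of the 16 cells are below 5, so the chi-square p is itself approximate here.

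**Table 2, four categories**: 8/10/5/3, 12/6/5/3, 14/3/6/3, 16/2/5/3.

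- Chi-square p = 0.325.
- ANOVA p from 0.025 to 0.837; 4 of 24 codings fall below 0.05.

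**Table 3, three categories A/B/C**: 10/6/10, 4/18/4, 10/6/10, 7/12/7. Column totals are 31, 42 and 31, so the smallest expected count is 31/4 = 7.75 and sparseness is not an issue.

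- Chi-square on 6 degrees of freedom: p = 0.015.
- Coding A=1, B=2, C=3: the group means are (10+12+30)/26 = 2, (4+36+12)/26 = 2, (10+12+30)/26 = 2 and (7+24+21)/26 = 2. All are equal, so F = 0 and p = 1.00.
- Coding A=2, B=1, C=3: the group sums are 56, 38, 56 and 47, total 197.
  - Between-group sum of squares: (56² + 38² + 56² + 47²)/26 − 197²/104 = 381.73 − 373.16 = 8.57.
  - Total of squared codes: 31·4 + 42·1 + 31·9 = 445. Within-group sum of squares: 445 − 381.73 = 63.27.
  - F = (8.57/3)/(63.27/100) = 4.51 on 3 and 100 degrees of freedom, p = 0.005.

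The same 104 assumed patients give no sign of imbalance or a clear one, by numbering alone.

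**Two categories**: 8/18, 12/14, 14/12, 16/10.

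- Chi-square p = 0.145; ANOVA p = 0.148 under either coding.
- Swapping two codes only reverses and shifts the scale, which leaves F unchanged. The dependence on codes therefore needs at least three categories.

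**The case against.** The best defence is that this is loose drafting: the gender sentence should also have named etiology, and an analyst would notice. That is plausible, but no other text in the article corrects it, so the rule stands as written.

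The other points on that side largely hold and limit the finding:

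- **The tables are assumed.** The range of p-values shows what can happen, not what will. If etiology were reduced to two categories, such as traumatic and non-traumatic, the problem would all but vanish. The article states no such reduction.
- **Nothing depends on the result.** A reader might infer that the error carries over to the trial's conclusions. The documents do not support that: no covariate is chosen from these tests, and the comparison of SWADOC scores across consciousness groups is an unadjusted ANOVA.
- **An imbalance would not disappear from view.** The section promises a description of etiology by group, whatever p-value stands beside it. Nor does the article say that etiology confounds the relation between consciousness and swallowing; that is a reader's inference.
- **Time since insult is not affected.** A reader might extend the criticism to this variable, because entry requires a "minimum of 28 days since the acquired brain injury at inclusion" with no stated upper limit, and because the section on swallowing and levels of consciousness has a Kruskal–Wallis fallback while this one has none. But the variable is continuous, the article gives no distribution for it, skew is only a guess, and Welch's version is provided for unequal variances. Preferring a rank test there is a matter of taste and does not show an error.

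**Conclusion.** The point holds in a limited form. The stated rule puts a nominal variable under ANOVA, Levene's test and Welch's approximation, none of which suits it. With three or more etiology categories the resulting p-value is arbitrary; with two it is practically harmless. The conclusion rests on the plain reading of the remaining-variables sentence and on etiology being recorded as categories. The illustrated sizes rest on assumed counts with equal groups of 26.

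Severity is minor. Only the descriptive test of etiology across groups is touched, and no figure in the article changes.

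**What to change.** Reword the test assignment in Descriptive Analysis so that:

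- gender and etiology are compared between groups with chi-square tests, using the Fisher–Freeman–Halton test or a Monte Carlo exact version where expected counts are small;
- age and time since insult keep the one-way ANOVA with Levene's test and the Welch fallback.

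The exact option is worth naming, since expected counts of 3.0 arise in both assumed four-category tables. The cost is one sentence: no extra patients, data or visits, and no effect on power.

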#### Reliability

The intrarater (i.e., SWADOC-scored vs. SWADOC-scored by the same examiner on the same day and on two different days) and interrater reliability (i.e., SWADOC-scored vs. SWADOC-scored on the same day by two different examiners) will be calculated in two separate analyses using weighted Fleiss's kappa coefficients (K_W_). A value below 0 will be considered to indicate poor agreement, between 0 and 0.2 slight agreement, between 0.21 and 0.4 fair agreement, between 0.41 and 0.6 moderate agreement, between 0.61 and 0.8 substantial agreement, and between 0.81 and 1 almost perfect to perfect agreement (32). We will also determine the internal consistency of the SWADOC-scored with Cronbach and Spearman intercorrelations to determine the interrelatedness of the constituent items.

#### Validity

##### Concurrent Validity

The results of the SWADOC-scored will be compared to the FOTT-SAS score for the same time and with the best score using Pearson's correlation (parametric test) or Kendall's correlations (nonparametric test) after examination of the data distributions.

##### Measures of Dispersion

The distribution of total SWADOC-scored scores will be examined to determine whether performance on the scale is evenly distributed across the range of possible scores, and each item will be analyzed to identify possible floor or ceiling effects. Based on these results, we will consider the need to modify the scale accordingly.

#### Relationship Between Swallowing Components and Levels of Consciousness

The differences in SWADOC-scored items, oral and pharyngeal subscores for the SWADOC-scored, and total score for the SWADOC-scored for the consciousness diagnostic groups will be assessed using a comparison of means with a one-way ANOVA. Violation of the homogeneity of variance will be checked using Levene's test. If this is the case, we will use Welch's approximation instead of an ANOVA. If there is a significant main effect, we will perform Tukey's honestly significant difference (HSD) test to compare all pairwise differences. If there is a severe violation of the normality, we will perform a Kruskal–Wallis test with the Dwass-Steel-Critchlow-Fligner (DSCF) multiple comparison analysis. Partial eta-squared will be used as a measure of effect size. *Post-hoc* multiple comparisons will be conducted to identify where significant differences between consciousness groups exist. SWADOC scores will be the dependent variable, while consciousness group will be the independent variable. Statistical analysis will be performed by a researcher blind to the consciousness category.

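### The level-0 expectation for UWS patients concerns a proportion, but the only item-level analysis stated compares group means and cannot test it

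*Protocol article*

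**What the plan says.** Three places in the protocol article bear on this.

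- **Introduction.** Validating the tool "will help us identify swallowing behaviors that may be considered unequivocal signs of consciousness in patients with DOC". The results may in time feed diagnostic guidelines. The same section reports that, in the earlier cohort, an effective oral phase was seen in no UWS patient and in only a minority of MCS patients.
- **Study Hypotheses.** The second hypothesis is that the subscores and total score are related to the level of consciousness. It adds an item-level expectation: UWS patients will be at level 0 on oral items 1, 3 and 4 (mouth opening as the spoon approaches, lip prehension, tongue propulsion).
- **Relationship Between Swallowing Components and Levels of Consciousness.** The analysis takes in the individual scored items as well as the two subscores and the total. Differences in all of these "for the consciousness diagnostic groups will be assessed using a comparison of means with a one-way ANOVA". Welch's version is used if variances differ, and a significant omnibus result leads on to Tukey's pairwise comparisons. For clearly non-normal data the plan changes method: "If there is a severe violation of the normality, we will perform a Kruskal–Wallis test". A rank-based multiple comparison procedure then replaces Tukey's. Partial eta-squared is the effect size.

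Power of the Study states that "a total sample size of 104 participants (26 per group) is needed".

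**The concern.** The level-0 expectation, and any claim that a behaviour is an unequivocal sign of consciousness, are statements about UWS patients alone: none, or almost none, of them show it. The quantity of interest is the proportion of UWS patients above level 0.

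The stated item-level tests have a different null hypothesis, namely that the four groups do not differ. Rejecting it shows that some group scores higher than another. It does not show that UWS patients score zero, and a significant post-hoc contrast between UWS and another group does not show it either. Failing to reject does not show that the behaviour lacks specificity. The floor and ceiling check under Measures of Dispersion does not close the gap: it is not described by diagnostic group, and its purpose is to decide whether to modify the scale.

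At stake is the reading of the item results. A stated expectation would reach the report with no analysis that answers it, and the p-value from the mean comparison would be the only item-level evidence at hand when signs of consciousness are discussed.

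**Working it through.** **1. Inputs.** From the article: four groups, 26 per group, items scored 0 to 3, a calculation "with a significance level of 0.05 and a power of 0.8", and the decision to "base our calculation on an effect size of 0.1, corresponding to an intermediate effect". The article does not give the share of each group showing a behaviour, so those shares are assumptions and are varied.

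**2. The plan's own figure.** Taking the effect size as eta-squared, f = √(0.1 / 0.9) = 0.333 and λ = N·f² = 104 × 0.111 = 11.56. The noncentral F with 3 and 100 degrees of freedom gives power 80.8%, and 104 is the smallest multiple of 4 reaching 80%. The stated 104 is reproduced, so 26 UWS patients is the planned number.

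**3. What the mean comparison does.** Simulation with 26 per group, alpha 0.05 and 8,000 runs per profile. Items were scored either as shown/not shown (binary) or as 0 versus an even mix of levels 1 to 3 (ordinal). The figures are the percentage of studies with a significant result, binary / ordinal.

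| Assumed share showing it, UWS/MCS–/MCS+/EMCS | ANOVA | Kruskal–Wallis |
|---|---|---|
| *Not specific* | | |
| 30/50/70/90% | 99.6 / 95.1 | 99.6 / 96.9 |
| 30/60/70/80% | 93.9 / 81.6 | 93.5 / 85.7 |
| 40/60/70/80% | 76.0 / 58.5 | 74.6 / 62.6 |
| *Fully specific, rare* | | |
| 0/5/5/5% | 7.7 / 6.8 | 6.3 / 6.9 |
| 0/10/10/10% | 16.8 / 13.1 | 14.1 / 13.7 |
| 0/15/15/15% | 30.2 / 24.3 | 29.1 / 30.5 |
| 0/5/10/20% | 54.3 / 48.6 | 50.9 / 52.9 |
| 0/20/20/20% | 56.9 / 41.6 | 54.3 / 54.3 |
| 0/0/10/20% | 85.2 / 70.5 | 74.0 / 74.7 |
| *Fully specific, commoner* | | |
| 0/10/20/30% | 83.1 / 73.1 | 82.5 / 82.3 |
| 0/30/30/30% | 96.7 / 87.1 | 95.7 / 94.9 |

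A significant Tukey contrast with UWS does not separate the cases. At 30/60/70/80% it occurs in 92.3 / 79.3% of studies; at 0/10/10/10% in 11.7 / 9.9%.

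So a significant result is compatible with 30% of UWS patients showing the behaviour, and a behaviour never shown in UWS can be missed when it is rare and spread over the conscious groups. Moving to Kruskal–Wallis does not change this.

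**4. What 26 UWS patients can show directly.** Exact (Clopper–Pearson) limits:

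- 0 of 26, two-sided 95%: upper limit = 1 − 0.025^(1/26) = 13.2%.
- 1 of 26, two-sided 95%: upper limit 19.6%.
- If 5% of UWS patients truly show the behaviour, the chance of seeing none is 0.95^26 = 26%.
- Excluding a 5% rate with a zero count (one-sided 95%) needs ln 0.05 / ln 0.95 = 58.4, so 59 UWS patients.

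**The case against.** The strongest reply is that the plan promises less than this point assumes. The sentence about unequivocal signs is background and is hedged: the tool will help identify behaviours that may be considered such signs. The stated aims, in the Abstract, Introduction, Study Hypotheses and Discussion, are about a relationship, and a comparison across groups fits that. On that question, rejecting at 30/50/70/90% is the right answer, not a false positive. All of this stands.

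A reader might infer that every significant item will be declared a sign of consciousness, so that unconscious patients would be labelled conscious. The document contains no such rule. It also ties the hope to qualitative as well as quantitative components, and 48 of the 56 items are qualitative and outside this analysis.

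A reader might also infer that the mean comparison generally misses specific signs. It does not: at 0/30/30/30% it detects them in 87–97% of studies. Even a rare sign is usually found if it is concentrated in the higher groups (0/0/10/20%: 70–85%).

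Finally, per-group item tables are often left to a full protocol or SAP, neither of which is shown. The mere absence of a table would be no finding. What remains is that the article states both an item-level expectation about UWS patients and an item-level method, and the method does not answer the expectation.

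**Conclusion.** The point holds as a mismatch between one stated expectation and the one stated item-level analysis, and as a caution about what may be concluded on signs of consciousness. It is not a fault in using ANOVA for the relationship hypothesis.

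Its size, under the assumed profiles: significance in at least 95% of studies with 30% of UWS patients showing the behaviour (30/50/70/90%), and detection of about 7–57% for a sign absent in UWS and shown by an equal 5–20% of each conscious group. The miss is therefore limited to signs shown by up to about 15–20% of conscious patients, and depends on how they are spread over the groups.

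The limit that needs no profile is the exact one: 0 of 26 leaves up to 13.2%. It assumes the planned 26 UWS patients are reached, and would be wider with fewer. A clean result in this sample can support a candidate sign but not an unequivocal one.

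**What to change.** 1. Keep the ANOVA, with its Welch and Kruskal–Wallis alternatives, for the hypothesis that scores are related to the level of consciousness.
2. For oral items 1, 3 and 4, report the number and proportion of UWS patients above level 0 with an exact 95% CI, alongside the proportions in MCS– and MCS+. Do the same for any other item put forward as a sign of consciousness.
3. Do not apply level 1 or higher as a common definition of present to all eight items. The level definitions are in a figure and supplement not shown here, and at least one item grades the amount of secretions. For an item beyond 1, 3 and 4, name in advance the level that counts as showing the behaviour.
4. Base any statement about a sign of consciousness on the UWS interval, not on the ANOVA p-value. No fixed specificity threshold is needed.
5. State that 0 of 26 UWS patients does not exclude a rate of up to 13.2%, and use the term candidate sign.

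The cost is one extra table from data already collected, and a more modest conclusion. No further patients or assessments are needed.
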